**Methods:**

Individual-level information linked across multiple administrative datasets will be used to conduct a series of retrospective observational studies on selected developmental and school outcomes. The predictor variables for all studies are the results from audiometric hearing assessments. The outcome measures are as follows: Australian Early Development Census results, representing developmental readiness for school, assessed around 5 years of age; Year 1 school attendance rates; Year 3 school-based academic performance, assessed in the National Assessment Program—Literacy and Numeracy; incidence of child maltreatment events (including both notifications and substantiated cases); and incidence of a first guilty verdict for youth offenders. Confounding and moderating factors available for the analysis include both community-level factors (including school fixed effects, socioeconomic status, level of remoteness, and housing crowdedness) and individual-level factors (including maternal and perinatal health and hospital admissions in early childhood).

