## Introduction

### Background

Children’s experiences during infancy and early childhood are critical to their health and educational and socioemotional well-being throughout their life course [1-5]. Through this period of rapid development, children are particularly sensitive to influences from their living environment [1,6]. At this age, the ability to hear is crucial to children’s normal development, as children learn to speak and communicate by imitating the sounds they hear, and hearing impairment (HI) is likely to reduce children’s exposure to sounds and voices and hamper their language development [7]. Consequently, delayed or impaired language learning can adversely affect children’s physical health, as well as social and emotional development [7-9].

Otitis media (OM) and the associated HI among Australian Aboriginal children has been extensively researched [10-19]. Community surveys conducted in Aboriginal children living in remote communities have consistently reported extremely high prevalence of OM, as high as 90% in some reports, which has persisted through decades of clinical and public health interventions [14,18-20]. Studies have also found that OM affects Aboriginal children early in life, is more severe, and persists for longer [7,10,21], with prevalence peaking at the young age of 5 to 9 months [15]. Among the affected children, if OM is left untreated or not treated adequately, it often progresses to chronic suppurative OM (CSOM) and tympanic membrane perforation, with mild to moderate conductive hearing loss [22-24]. The impact of HI on language development may be compounded in Aboriginal children, when English is a second or third language, but school-based teaching relies on English [22,25-28]. In this setting, it may be reasonably expected that OM-related HI may directly or indirectly impact children’s readiness for school and subsequent participation and performance at school, as well as their ongoing social and behavioral development through childhood and adolescence.

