### The Study Cohort

The study cohort comprises NT-born Aboriginal children, with hearing assessment results in the RHA dataset and with a residential location classified as *remote* or *very remote* on the basis of ARIA+ [48]. Further inclusion and exclusion criteria will vary among the component studies of this study, depending on the respective requirements. In principle, as the data analysis will be based on a complete-case analysis, only children with data in the selected dependent, outcome, and control variables will be included. Children who have had surgical treatment for OM before the age of 4 years will be excluded, as the surgery could alter the impact of HI during the early childhood period. This will be done by searching in another linked administrative dataset, the NT Hospital Separations Dataset, and excluding children admitted before the age of 4 years, with any diagnosis code plus any procedure code related to OM and its treatment (Table 1).

**Table 1 table1:** Otitis media—related hospital admission diagnoses and surgical procedures used to exclude children who had received surgical treatment, with International Classification, 10th Revision-Australian Modification codes.

ICD-10AM^a^ Code		Diagnosis/procedure

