#### Child Maltreatment

The data source for this study is the NT Government Child Protection dataset, which is a statutory data collection of child maltreatment—related contacts with child protection services. The research dataset will include information on all notifications (reports), substantiated cases, and episodes of out-of-home care. The outcome measures for this study will be the cumulative incidence of first notification of child maltreatment and the cumulative incidence of first substantiated case of child maltreatment. The time to event will be calculated from date of birth to the earliest of the following: date of each event of interest, date of death, the last observed date in the linked datasets, or the designated end of follow-up date for the study. Data are available from 1999 to 2017.

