### Control Variables

The selection of control variables will vary between studies and the availability of the relevant variables in the linked datasets. We will draw reference from published literature in selecting control variables known to have confounding or moderating effects on the association being investigated. Individual-level control variables will be retrieved from the linked health, education, child protection, and justice datasets, including maternal and perinatal factors from the Perinatal Registry dataset (a statutory collection containing information for all births in the NT), as well as hospital admission diagnoses from the NT Hospital Separation Dataset. Community-level factors will include relative level of geographic remoteness (as measured with ARIA+), housing crowdedness (as measured with average household size and average persons per bedroom in the community), and socioeconomic disadvantage (as measured with the Index of Relative Socio-Economic Disadvantage) [48,50,64]. Aggregated data on these factors will be combined with the linked administrative datasets, using the relevant location variable for each study (either community of residence or school location).

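### Maltreatment follow-up starts at birth, but surgery up to age 4 removes the whole child, so early events are kept or dropped on later information

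*Protocol article*

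**What the plan says.** Methods, Child Maltreatment, sets the time scale: "The time to event will be calculated from date of birth to the earliest of the following", the end points being the event, death, the last date observed in the linked data, or the end of follow-up. The outcomes are the "cumulative incidence of first notification of child maltreatment" and the same measure for a first substantiated case.

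Methods, The Study Cohort, sets eligibility: "Children who have had surgical treatment for OM before the age of 4 years will be excluded". The reason given is "as the surgery could alter the impact of HI during the early childhood period". Surgery is identified from an admission carrying both a diagnosis code and a procedure code from Table 1. The section adds that "Further inclusion and exclusion criteria will vary among the component studies of this study", but exempts no component from the surgery rule.

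On covariates, the Abstract lists, among factors available to the analysis, "individual-level factors (including maternal and perinatal health and hospital admissions in early childhood". Control Variables names perinatal data, "as well as hospital admission diagnoses from the NT Hospital Separation Dataset", and community factors, and leaves the choice to each component study. The Statistical Analysis Plan section specifies Cox models for maltreatment and offending. It mentions no delayed entry, landmark or time-dependent covariate.

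**The concern.** The maltreatment clock opens at age 0, while the exclusion is not settled until age 4. Within that window a child's person-time and any first event stay in or drop out according to surgery that may come after the event. A Cox model needs risk-set membership at each age to depend only on what has happened by then, and this rule breaks that.

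Only maltreatment is affected. The developmental census (about age 5), Year 1 attendance (about 6-7) and Year 3 tests (about 8) all come after the window, and the offending clock starts at the 10th birthday. A rule that suits those components has been carried over to one whose follow-up overlaps it.

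At stake are the HI hazard ratios for first notification and first substantiation. If notified children become more, or less, likely to have ear surgery, their early events are removed at a different rate from the person-time of children not notified. Because surgery is presumably commoner with HI, that loss would differ between the groups being compared.

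**Working it through.** **1. The windows side by side.** Origin: age 0. Exclusion window: age 0 to under 4, whole child removed. For an event at age t < 4, eligibility therefore depends on surgery over (t, 4). This follows from the two stated rules and needs no assumption.

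**2. Inputs for size.** The protocol gives no surgery frequency, event rate or effect size, so there is no figure of its own to reproduce. All of the following are assumptions: surgery before age 4 in 11% of children with HI and 6% of others; notification hazard 0.045 per year without HI; half the cohort with HI; follow-up to age 12; true HI hazard ratio 1.3 or 1.0; notification multiplies the later surgery rate by k = 0.5, 1, 2 or 4.

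**3. Retention.** With surgery rate λ, a child event-free to age 4 is kept with probability exp(−4λ). A child with an event at t is kept with probability exp(−λt − kλ(4 − t)). The ratio is exp(−(k − 1)λ(4 − t)).

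- λ with HI = −ln(0.89)/4 = 0.0291; λ without = −ln(0.94)/4 = 0.0155; difference 0.0137 before rounding.
- k = 1: the ratio is 1 in both groups, so there is no bias.
- k = 2, event at age 1: exp(−0.0291 × 3) = 0.916 with HI and exp(−0.0155 × 3) = 0.955 without. Relative retention is 0.916/0.955 = 0.96.

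**4. Averaging over follow-up.** The mean of 4 − t for events before age 4 is about 2 years. Their share of all events without HI is (1 − exp(−0.18))/(1 − exp(−0.54)) = 0.165/0.417 = 0.39, and slightly more with HI, so about 0.40. The approximate shift in the log hazard ratio is −(k − 1) × 0.0137 × 2 × 0.40:

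- k = 0.5: +0.005
- k = 1: 0
- k = 2: −0.011
- k = 4: −0.033

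**5. Check by simulation.** 3,000,000 children per row; standard error of the log hazard ratio about 0.002.

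| True HR | k | Surgery before 4 excluded | Censored at first surgery |
|---|---|---|---|
| 1.3 | 0.5 | 1.308 | 1.301 |
| 1.3 | 1 | 1.301 | 1.301 |
| 1.3 | 2 | 1.287 | 1.299 |
| 1.3 | 4 | 1.264 | 1.300 |
| 1.0 | 0.5 | 1.006 | 1.000 |
| 1.0 | 1 | 1.000 | 1.000 |
| 1.0 | 2 | 0.990 | 0.999 |
| 1.0 | 4 | 0.971 | 0.999 |

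The exclusion gives about 0.5% higher at k = 0.5, no change at k = 1, about 1% lower at k = 2 and about 3% lower at k = 4. Censoring recovers the true value in every row.

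**The case against.** The strongest reply is that nothing in the protocol links notification to later surgery, and without that link the look-ahead does no harm. That stands: at k = 1 the bias is nil, and even at k = 4 it is small. What remains is that the plan relies on an independence it neither states nor tests, when a design that does not need it is available from the same records.

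Three stronger readings are tempting, and the protocol does not support them.

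- A reader might infer that the hazard ratio is pulled toward or below 1. The direction follows from k: above 1 it falls, below 1 it rises, and k is unknown.
- A reader might infer that the maltreatment model adjusts for early-childhood admissions as fixed covariates, so that an admission at age 3 could account for a notification at age 1. Admissions are only listed as available, controls vary by component, and neither an age window nor the coding is given. Such detail may properly sit in a fuller document. The criticism applies only if they are entered that way, although the univariate P<.25 screen would tend to keep a variable whose association came from reversed timing.
- A reader might infer that starting at birth dilutes the effect with months before hearing loss can act. That is a separate matter. The share of notifications so early is not given, OM is described "with prevalence peaking at the young age of 5 to 9 months", and the plan assumes that the first hearing test represents long-term hearing.

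It is also fair to say that cohort entry requires a hearing test at any age, which looks ahead as well. Correcting the surgery rule does not cure that.

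**Conclusion.** The inconsistency is certain: the maltreatment models start at birth, but eligibility is settled by surgery up to age 4. Its effect on the HI hazard ratio is conditional and modest. It is nil if notification does not change later surgery, and otherwise up to about 3% in either group of scenarios (true hazard ratio 1.3 or 1.0), with the sign set by whether surgery becomes more or less likely. These sizes rest on the assumed 11% and 6% surgery frequencies, a constant notification hazard and k between 0.5 and 4. Larger surgery differences or a stronger link would give more. The point deserves correction because the change is cheap, not because it threatens the main conclusion.

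**What to change.** For the maltreatment component only:

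1. Replace the exclusion for surgery before age 4 by censoring at the date of the first admission meeting the Table 1 definition, keeping all earlier time and events. This still serves the stated reason for the rule, since time after surgery is not used.
2. Report the analysis with the exclusion as a sensitivity analysis, so that readers can see whether it matters.
3. If hospital admissions are used as controls in these models, enter them as time-updated from the admission date, not as a fixed early-childhood indicator.

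The cost is wording and episode splitting of records already linked. There are two downsides: censoring assumes surgery is non-informative given the covariates, and the maltreatment cohort will differ slightly from those of the other components. Starting the risk period at age 4 among children still event-free would also remove the look-ahead, but it discards every earlier event. In a separate illustration with an assumed constant hazard, that was 46% of events by age 10.

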#### Youth Offending

The Youth Justice dataset was provided by the NT Department of the Attorney-General and Justice, and this contains records of youth offending in the NT. The outcome measure for this study will be the cumulative incidence of first episode of a proven guilty offence within the youth justice system. The starting point for follow-up will be the 10th birthday, which is the minimum legal age of criminal responsibility, and the follow-up time will be calculated to the date of first offence or censored at the date of death, the last observed date in the linked datasets, or the set endpoint for follow-up of this study. Data are available for the period 1997 to 2017.

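### Follow-up in the two Cox studies ends at an undefined last observed date which, read as each child's own last record, inflates cumulative incidence and can bias the hearing impairment hazard ratios if record contact differs by hearing level

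*Protocol article*

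**What the plan says.** In the Child Maltreatment section, "The time to event will be calculated from date of birth to the earliest of the following: date of each event of interest", and the remaining end points are "date of death, the last observed date in the linked datasets, or the designated end of follow-up date for the study".

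In the Youth Offending section, "The starting point for follow-up will be the 10th birthday", and a child without an offence is "censored at the date of death, the last observed date in the linked datasets, or the set endpoint for follow-up of this study".

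Both sections name cumulative incidence of a first event as the outcome measure. The Statistical Analysis Plan section assigns Cox models to these two studies, which serve the fourth and fifth hypotheses in the Objectives. The Control Variables section describes the data as "linked health, education, child protection, and justice datasets", so both outcome registers are part of the linked set.

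The data windows differ. For child protection, "Data are available from 1999 to 2017"; for youth justice, "Data are available for the period 1997 to 2017". School attendance and NAPLAN end in 2016 and the hearing assessments in 2015. The article gives neither the hospital data window nor the date on which follow-up ends.

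**The concern.** The last observed date stands beside the child's own event and death dates and apart from the study end date. If it meant only the data cut-off, it would largely duplicate the last item in the list. So it most naturally means the last date on which that child appears in any linked dataset.

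Read this way, the rule treats children differently according to their outcome. Take two children with the same long gap in their school, hospital and hearing records. One offends late in the gap: the offence is a linked record, so follow-up runs to it and the event counts. The other never offends: follow-up stops where the gap begins. Event-free time is removed only from children without events.

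Two things are at stake. Cumulative incidence is overstated whatever the role of HI. The hazard ratio for HI is distorted as well if the amount of time removed differs between hearing groups.

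**Working it through.** The article gives no sample size, event count, incidence, hazard ratio or record frequency for these outcomes, so there is no figure to reproduce. All rates below are assumptions.

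**Inputs (offending).** Constant hazard h = 0.04 per year from age 10; potential follow-up T uniform between a = 0.5 and b = 8 years; the gap between the last record and the end of follow-up exponential with rate r records per year, cut off at the start of follow-up.

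**Formulas.** Let E(k) = (e^(−ka) − e^(−kb)) / (k(b − a)).
- Events per child: D = 1 − E(h)
- Full person-time per child: P = D/h
- Person-time lost by event-free children: L = (E(h) − E(h + r))/r
- Rate under the rule: D/(P − L)

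**Numbers.** E(0.04) = (0.9802 − 0.7261)/0.30 = 0.8468, so D = 0.1532 and P = 0.1532/0.04 = 3.829 years.

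| Records per year, r | E(h + r) | L (years) | Rate D/(P − L) |
|---|---|---|---|
| 0.5 | 0.1852 | 1.323 | 0.0611 |
| 1 | 0.0762 | 0.771 | 0.0501 |
| 4 | 0.0044 | 0.211 | 0.0423 |
| 20 | about 0 | 0.042 | 0.0404 |

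The true rate is 0.0400. Simulation of 400,000 children per scenario gave 0.0614 at r = 0.5 and 0.0498 at r = 1, in agreement.

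**Cumulative incidence (simulation, true hazard ratio 1.0).** The true values are 1 − e^(−0.04 × 7) = 24.4% for offending and, with an assumed 0.05 per year and 4 to 18 years of follow-up, 1 − e^(−0.05 × 17) = 57.3% for maltreatment.

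| Records per year | Offending at 7 years: rule vs full observation | Maltreatment at 17 years: rule vs full observation |
|---|---|---|
| 4 | 26.2% vs 24.5% | 58.8% vs 57.3% |
| 1 | 32.3% vs 24.4% | 64.0% vs 57.2% |
| 0.5 | 41.1% vs 24.5% | 70.4% vs 57.3% |

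**Hazard ratio, equal contact.** With the same record rate in both hearing groups there was essentially no bias: offending at 1 per year, 1.296 against 1.301 under full observation; at 0.5 per year, 1.327 against 1.339.

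**Hazard ratio, unequal contact.** From the table, with a true ratio of 1.0 and 0.5 (normal hearing) against 1 (HI) record per year, the rate ratio is 0.0501/0.0611 = 0.82; reversed, it is 1.22. The Cox fits gave 0.81 and about 1.24. With a true ratio of about 1.3 and HI children contacted twice as often:

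| Records per year (normal, HI) | Offending: rule vs full observation | Maltreatment: rule vs full observation |
|---|---|---|
| 0.5, 1 | 1.04 vs 1.30 | 1.20 vs 1.30 |
| 1, 2 | 1.17 vs 1.32 | 1.25 vs 1.30 |
| 2, 4 | 1.22 vs 1.29 | 1.27 vs 1.30 |
| 10, 20 | 1.28 vs 1.30 | 1.30 vs 1.30 |
| 20, 40 | 1.30 vs 1.30 | 1.30 vs 1.30 |

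**Earlier end of the other data.** If non-outcome records stop one year before the outcome data, even dense records (20 against 40 per year, true ratio 1.3) leave the offending rate at 5.7% against 4.6% per year, while the hazard ratio moves only from 1.29 to 1.27. At 4 records per year the rate is 6.0% against 4.6%. The 7-year incidence there reaches 55.8% against 27.5%, but 7 years is the last point at which any event-free child can still be under observation (8 − 1), so the rate is the fairer summary.

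**Symmetric rule.** Ending follow-up at the last non-outcome record and ignoring later events brought incidence and hazard ratio back to about their true values in every scenario. For offending at 1 against 2 records per year, the hazard ratio was 1.32 (full observation 1.32) and 7-year incidence 27.6% (27.4%). Record contact in the simulation did not itself depend on the outcome.

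**The case against.** - **The reading is inferred.** Neither section says the date is the child's own, nor which datasets count. If it means the cut-off of the data extract, the problem disappears. If it is computed from non-outcome data and the earliest date is applied literally, later events are dropped and the rule is the symmetric one. This stands, and it is why the point is conditional. But a term that fixes person-time in two analyses should not depend on the reader's choice.
- **A reader might infer that events count without limit and that the HI hazard ratios are biased as a matter of course.** The documents support neither. The end-of-follow-up date still caps events, and with equal contact the hazard ratio was right even where incidence was badly inflated. The article gives reasons why contact might differ (need-based access to hearing services from January 2013; the hypothesis that HI lowers attendance), but no contact rates by hearing level. Those reasons point in opposite directions: more service contact pulls the ratio down, less school contact pushes it up.
- **Records may be dense.** The attendance dataset holds daily status, so enrolled children may have many dated records a year and the distortion may be negligible. This stands for school years in government schools up to 2016. It does not cover other schools, children out of school or the year 2017.
- **The 2016 to 2017 lag may be smaller than modelled.** Hospital data may run to 2017, child protection records can serve as observations in the offending study, and an end date at or before the end of 2016 would remove the lag against the education data. The article does not settle these points.
- **Last-contact censoring has a purpose.** The outcome registers cover the Territory only. With an assumed 3% a year leaving, censoring everyone at the administrative end understated 17-year maltreatment incidence (50.5% against 62.1%). Simply deleting the last-observed rule is therefore a trade-off.
- **An article condenses the plan.** The working definition may be in a fuller document. But the rule printed here is, on its natural reading, a faulty one and not merely a brief one.

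**Conclusion.** The point holds conditionally. If the last observed date is each child's own last record and the outcome registers count as observations, censoring depends on the outcome and cumulative incidence is overstated in both studies. Under the assumed rates with no lag, the excess runs from 1 to 2 percentage points at four records a year to 13 (maltreatment) or 17 (offending) at one record every two years, and is smaller still with denser records. Inflation persists with dense records where the other data stop before the outcome data.

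Bias in the HI hazard ratios needs contact that differs by hearing level. It is then negligible with dense records and large with sparse ones: a true 1.3 for offending falls to about 1.04 in the sparsest case examined. The documents establish neither its direction nor its presence. This should be corrected before the two Cox analyses are run.

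**What to change.** In both the Child Maltreatment and Youth Offending sections, define the end of follow-up without reference to that study's outcome records. There are two acceptable rules:

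1. End every child's follow-up at the last record in the datasets other than that study's outcome register, and do not count events after that date, so that children with and without events are treated alike.
2. Censor every event-free child at death or at one fixed calendar date to which the outcome register is complete.

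Make one primary and the other a sensitivity analysis. State the calendar end date, and name the datasets that supply the last record with the years they cover. A table of non-outcome records per child-year by HI category would show whether differential contact is a practical concern.

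The cost is a few sentences and a few lines of code. The first rule drops some late events and assumes that contact with the other services is not driven by the outcome. The second keeps children who have left the Territory at risk. Running both shows how far the results depend on the choice.
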